## Materials and methods

Participant allocation will be concealed using sequentially numbered, opaque, sealed envelopes, prepared prior to the study by a research assistant who will not be involved in data collection or analysis. After obtaining baseline measurements, participants will be randomly assigned to either the experimental or control group. A separate research assistant will be responsible for setting the stimulator to active TMS or placebo, ensuring that the therapists administering the intervention remain blinded to group allocation. All outcome assessments will be conducted by blinded evaluators.

Participants will be allocated to either the active stimulation or placebo (sham) group. Both groups will undergo TMS to collect motor-evoked potential (MEP) data, which will be used to calibrate individual stimulation parameters. This procedure will be supported by electromyography (EMG) to ensure data accuracy.

On the first day of testing, following MEP data collection, all participants will undergo a familiarization period with the isokinetic dynamometer. During this session, they will perform practice tests to become acquainted with the equipment, followed by isokinetic assessments at speeds of 30°/s and 60°/s, with five repetitions at each speed. After a five-minute rest period, an additional test will be conducted before and after TMS application, consisting of 50 repetitions at a speed of 180°/s. To assess the coefficient of variation during testing, participants will not be informed of the number of repetitions in advance. This procedure will be repeated on both the first and fifth days of stimulation.

In the active group, TMS will be delivered using a Cool B70 butterfly coil (Magventure, Denmark) positioned over the primary motor cortex. Stimulation intensity will be set at 100 % of the motor threshold, defined as the lowest intensity capable of inducing peripheral muscle contraction, verified via EMG. The stimulation protocol will follow the 10/20 EEG system, with Cz serving as the common stimulation site for all participants. Coil orientation will depend on the dominant limb: for right-leg-dominant participants, the coil will be tilted 45° to the left, while for left-leg-dominant participants, it will be tilted 45° to the right. The protocol will consist of 30 trains of 100 pulses at 20 Hz, with each train lasting 5 s and separated by a 20-second inter-train interval, totaling 3000 pulses over approximately 20 min. This procedure will be repeated for five consecutive days, with individual motor threshold reassessed daily to ensure accurate stimulation parameters.

The placebo group will receive sham stimulation using a Cool B70 butterfly coil (Magventure, Denmark) designed to replicate the sound and timing of active stimulation without delivering a magnetic current.

On the fifth day, following stimulation, both groups will rest for five minutes before performing the same isokinetic dynamometer test as on the first day. The collected data will be compared with pre-stimulation results.

The study will be conducted at the School Clinic of the Federal University of Espírito Santo (UFES). All team members will receive standardized training on the use of the isokinetic dynamometer and TMS equipment. The TMS operators will remain blinded to group allocation, as the stimulator will be pre-configured by an external researcher with no direct contact with participants or investigators. During both isokinetic tests, participants will be instructed to exert maximum effort throughout all repetitions, with auditory stimuli provided to maintain engagement during testing.

Participants unable to complete the test will be classified as "incomplete tests," and a replacement participant will be recruited.

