## Sample calculation

To date, no studies have assessed the effects of TMS on large muscle groups, such as the quadriceps, using an isokinetic approach. Additionally, no established clinically significant difference exists for isokinetic quadriceps strength.

For this study, the effect size (Cohen’s f) for the statistical calculation of a two-way (between-within) ANOVA with two groups and two time points was set at 0.20. The following parameters were applied: effect size = 0.20, alpha = 0.05, statistical power = 80 %, number of groups = 2, number of measurements = 2, correlation between repeated measures = 0.5, and non-sphericity correction = 1. Based on these parameters, 42 volunteers were required. Considering a potential 20 % sample attrition, the final sample size was adjusted to 50 participants, with 25 allocated to the sham group and 25 to the intervention group (Table 1).

**Table 1 tbl0001:** Inclusion and exclusion criteria study.

Inclusion criteria	Exclusion criteria
1. Men aged between 18 and 50 years.	1. Have had deep brain stimulation (DBS) surgery.
2. Identified as sedentary or minimally active according to the IPAQ questionnaire.	2. Presence of associated neurological diseases.
3. Physically capable of performing isokinetic dynamometer tests.	3. Orthopedic conditions that limit participation in study.
4. Be able to understand instructions for the isokinetic dynamometer tests.	4. History of seizures or traumatic brain injury.
5. Scoring adequately on the Mini-Mental State Examination, adjusted for educational level (26 for higher education, 18 for primary and secondary education, 13 for illiterates).	5. Acute strain (musculotendinous unit) or sprain (non-contractile tissue).
6. Able to give informed consent in accordance with institutional policies.	6. Soft tissue healing restrictions (e.g., post-surgery).
7. Capable of completing all physical and cognitive test requirements as defined.	7. Pain during protocol execution.
	8. Extremely limited range of motion (ROM).
	9. Severe effusion.
	10 Joint instability.
	11. Subacute or chronic third-degree sprains.
	12. Significant knee ROM limitation.
	13. Lower limb joint laxity.

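### The protocol does not settle which strength tests are done when, or which pre/post comparison, speed and parameter the sample size calculation powers

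*Protocol article*

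**What the plan says.** All of this is in the Protocol article.

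- **Sample calculation** bases the size on a "two-way (between-within) ANOVA with two groups and two time points was set at 0.20", with "number of groups = 2, number of measurements = 2". The other inputs are "effect size = 0.20, alpha = 0.05", 80% power, and "correlation between repeated measures = 0.5, and non-sphericity correction = 1". The result is 42 volunteers, raised to 50 for attrition. It does not say which strength measurement the effect size refers to.
- **Materials and methods, first-day testing paragraph,** lists five repetitions each at 30 and 60°/s. After a rest, "an additional test will be conducted before and after TMS application, consisting of 50 repetitions" at 180°/s. The paragraph closes: "This procedure will be repeated on both the first and fifth days of stimulation".
- **Materials and methods, day-5 paragraph,** says that after stimulation "both groups will rest for five minutes before performing the same isokinetic dynamometer test as on the first day". The data are then compared with the results from before stimulation, with no day given.

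**The concern.** The three places describe different sets of measurements.

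Staff who follow the first-day testing paragraph would run a 180°/s test before stimulation on day 5. Staff who follow the day-5 paragraph might not. An analysis plan cannot repair this afterwards, because it decides which data exist.

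The open baseline changes the question as well as the bookkeeping. Day-5 post against day-1 pre asks what five daily sessions do. Day-5 post against day-5 pre asks what the last session does acutely, and it subtracts any gain carried over from days 1 to 4. If five sessions build strength gradually, the second contrast could show little even though the treatment works.

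The stated question is lower limb muscle strength, and three speeds are measured. With none of them tied to the calculation, a reader of the final report could not tell which result the trial was sized for.

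**Working it through.** **Step 1. The plan's own figure.** The inputs from Sample calculation are f = 0.20, alpha = 0.05, k = 2 groups, m = 2 measurements, rho = 0.5 and non-sphericity correction 1. For the group-by-time interaction:

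- noncentrality = f² × N × m / (1 − rho), with 1 and N − 2 degrees of freedom
- N = 42: 0.04 × 42 × 2 / 0.5 = 6.72, power 71.6%
- N = 50: 0.04 × 50 × 2 / 0.5 = 8.00, power 79.1%
- N = 52: 0.04 × 52 × 2 / 0.5 = 8.32, power 80.7%

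The stated inputs therefore give 52, not 42. That is a separate point, and nothing below depends on how 42 was reached.

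**Step 2. Occasions, side by side.**

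| Occasion | Sample calculation | First-day testing paragraph, 180°/s | First-day testing paragraph, 30 and 60°/s | Day-5 paragraph |
|---|---|---|---|---|
| Day 1, pre | two time points, not named | yes | yes, timing relative to stimulation not stated | possible reference |
| Day 1, post | | yes | unclear | not mentioned |
| Day 5, pre | | yes | unclear | not mentioned; possible reference |
| Day 5, post | | yes | unclear | yes, the same test as on day 1 |

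For 180°/s the count is 2 tests per day × 2 days = 4. For 30 and 60°/s the wording that places tests before and after stimulation is attached only to the 50-repetition test, so the count is open. Whether the day-5 post-stimulation test includes all three speeds depends on what the same test as on day 1 covers.

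**Step 3. What the choice of baseline estimates.** Let G be the gain carried into day 5 from sessions 1 to 4, and A the acute effect of session 5, each as active minus sham.

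- Day-5 post minus day-1 pre = G + A
- Day-5 post minus day-5 pre = (G + A) − G = A

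**Step 4. Scale of the unnamed speed.** Suppose, for illustration only, that each of three speeds is tested at 0.05.

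- Independent tests: 1 − 0.95³ = 14.3%
- Equally correlated normal test statistics, by simulation (400,000 draws): about 12.5% at correlation 0.5, 11.0% at 0.7 and 8.4% at 0.9

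These correlations are assumed; the document gives none between speeds.

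**Step 5. What a baseline-adjusted comparison gains.** With two time points and equal variance σ² at each, the mixed-ANOVA interaction is the same test as a two-sample comparison of change scores.

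- Change-score variance: 2σ²(1 − rho) = 2σ²(0.5) = σ²
- Baseline-adjusted variance: σ²(1 − rho²) = σ²(1 − 0.25) = 0.75σ²
- Ratio: 0.75, that is 25% less variance
- Noncentrality at N = 42: 6.72 / 0.75 = 8.96; with 1 and 39 degrees of freedom, power is 83%, against 72% for the change-score test

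**The case against.** The strongest reply is that the text already points to one comparison. Baseline measurements come before randomisation, hence before any stimulation. The day-5 test is described as a repeat of the first-day test. The Abstract and Background speak of data before and after the intervention, and the intervention is five daily sessions. Day-1 pre against day-5 post also fits the two time points in the calculation. This stands as a statement of where the text leans. It does not exclude a day-5 baseline, because the first-day testing paragraph schedules a day-5 pre-stimulation test and the day-5 paragraph does not date its reference. The study flowchart, which might settle it, is not visible.

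It is also fair that measuring on more occasions than were powered is ordinary practice. The extra occasions are no fault in themselves. The fault is that the sections disagree about them and that the powered pair is not named.

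Three stronger readings are tempting, and the document does not support them:

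- **That the trial will test every speed and contrast at 0.05.** No section says so; Sample calculation describes one ANOVA. Rules for multiple tests may sit in an analysis plan that is not shown. A count of three speeds by two contrasts also goes beyond the text, since repeated pre/post testing is explicit only for 180°/s.
- **That 42 shows a different number of occasions was entered.** Three measurements would give 42, but so would a correlation of 0.6, alpha of 0.10 or f of about 0.225. The document shows none of these.
- **That a 50-repetition bout before stimulation on day 5 biases the result.** It would fall on both randomised arms alike, so it does not by itself bias active versus sham.

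**Conclusion.** The point holds as an internal mismatch. Sample calculation uses two time points. The first-day testing paragraph gives four occasions for 180°/s and an unclear number for 30 and 60°/s. The day-5 paragraph mentions one post-stimulation test and an undated reference. The likeliest intended contrast is day-5 post against day-1 pre, but the text does not fix it, and the alternative answers a different question. No speed or parameter is identified as the one powered.

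The false-positive range of about 8% to 14% rests on two assumptions: that all three speeds would be tested at 0.05, and that their correlations lie between 0 and 0.9. It shows the scale of leaving the choice open and is not a property of the plan as written. The 25% variance reduction rests on the plan's own correlation of 0.5 and on equal variance at the two occasions.

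This should be corrected before testing starts, because an occasion that was not measured cannot be recovered later.

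**What to change.** 1. Make Sample calculation and both testing paragraphs of Materials and methods list the same occasions and speeds. State for each of 30, 60 and 180°/s whether it is tested before and after stimulation on day 1 and on day 5.
2. Name one primary comparison: active versus sham at day-5 post-stimulation, adjusted for the day-1 pre-stimulation value.
3. Have the investigators choose one speed and one parameter for it before unblinding, from those measured at both occasions. Peak torque at 60°/s is one option if that speed is scheduled after stimulation on day 5; the document does not single it out.
4. Say in Sample calculation that this is the comparison being powered. A baseline-adjusted analysis is not the mixed ANOVA now described, so that sentence needs to change too.
5. Label the other speeds, day-1 post and day-5 pre as secondary.

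The cost is wording only, provided the chosen speed is already tested at both occasions; otherwise one test is added. The downside is that the other speeds and occasions cannot carry the headline claim.

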### International Physical Activity Questionnaire (IPAQ)

The International Physical Activity Questionnaire (IPAQ) is a five-section, standardized tool designed for quick and facilitated application. It assesses participants' habitual physical activity levels by evaluating the frequency and duration of physical activities performed in daily life (Fig. 2).

**Fig. 2 fig0002:**
[figure not shown]

[figure not shown]

[figure not shown]

[figure not shown]
IPAQ- international physical activity questionnaire.

### Surface electromyography (sEMG)

Surface electromyography (sEMG) is a widely used research tool for quantifying neural control strategies that adapt to environmental and task-specific demands [6]. These strategies represent the signal output from the central nervous system (CNS) to execute movements via the peripheral nervous system (PNS) [6]. sEMG is a non-invasive technique that utilizes surface electrodes to measure muscle activity.

The amplitude of the sEMG signal is determined after an initial processing stage, which involves filtering and computing parameters such as the rectified mean square value, integrated value, or root mean square (RMS) from the raw data [6]. It is important to note that variations in electromyographic signal amplitude occur among individuals due to physiological and non-physiological factors, as well as detection variables that may influence data interpretation [6].

In this study, sEMG will be used to record motor potentials from the dominant lower limb’s quadriceps muscles, specifically the rectus femoris, vastus medialis, and vastus lateralis**.**

During data collection, participants will be positioned in a semi-recumbent posture, between sitting and supine. Electrode placement will follow the SENIAM (Surface Electromyography for the Non-Invasive Assessment of Muscles) guidelines, with the following anatomical references:•**Rectus femoris**: Electrodes will be positioned at 50 % of the distance between the anterior superior iliac spine (ASIS) and the superior border of the patella.•**Vastus medialis**: Electrodes will be positioned at 80 % of the distance between the ASIS and the joint space at the anterior edge of the medial ligament.•**Vastus lateralis**: Electrodes will be positioned at ⅔ of the distance between the ASIS and the lateral border of the patella.

This standardized electrode placement ensures reproducibility and accuracy in sEMG measurements, contributing to the reliability of the study (Figs. 3 and 4).

**Fig. 3 fig0003:**
[figure not shown]
Isokinetic dynamometer- biodex.

**Fig. 4 fig0004:**
[figure not shown]
Surface Electromyography equipament miotool.

### Protocol validation

The combination of non-invasive transcranial magnetic stimulation (TMS) with isokinetic dynamometry is expected to yield favorable results in assessing muscle performance parameters. This finding holds significant societal relevance, as positive outcomes could pave the way for further research aimed at refining this intervention for both healthy individuals and specific populations with distinct clinical needs.

## Limitations

The primary limitation of this study relates to the sample population, as it includes only male participants aged between 18 and 25 years. This restriction may lead to differences in outcomes if the study is replicated in populations with different characteristics, such as women, younger individuals, or older adults.

Furthermore, research on the effects of TMS on lower limb muscle strength remains scarce. The limited number of existing studies often fails to account for interindividual variability in responses to TMS, which may affect the generalizability of findings. Another major challenge is the lack of standardization in TMS protocols. Variations in stimulation parameters—such as intensity, frequency, and the number of sessions—can significantly impact results, complicating both interpretation and reproducibility across different populations and research settings.

Additionally, controlling all variables that influence TMS response poses a challenge. Factors such as participants’ baseline physical conditioning, pre-existing musculoskeletal injuries, or medication use can affect lower limb muscle strength and responsiveness to stimulation, potentially confounding study results.

Despite these limitations, this protocol remains both valid and necessary. The clinical hypothesis suggests that TMS may effectively enhance lower limb muscle strength, offering potential applications in rehabilitation and performance optimization. The findings of this study could contribute to the development of novel therapeutic strategies across various populations, emphasizing the importance of further investigation in this field.

## Disponibilidade de dados

None of the data described in the article has been used in research.

## Data Availability

Data will be made available on request.
